**Figure 2 figure2:**
[figure not shown]
Dietary decision support system workflow.

**Figure 3 figure3:**
[figure not shown]
Administrative control panel: entry of study participant demographics.

**Figure 4 figure4:**
[figure not shown]
Administrative control panel: addition of food categories.

**Figure 5 figure5:**
[figure not shown]
Administrative control panel: generation of personalized dietary feedback.

### Study Enrollment and Data Collection Procedure

Data were collected at baseline, and follow-ups were conducted at months 3 and 6, resulting in 4 data collection time points. After each time point, the field-workers scheduled follow-up interviews to administer the study questionnaires. The study staff who were collecting data were blinded to the group assignments.

### Informed Consent

Informed consent forms were administered to the eligible individuals, and those who consented were enrolled in the study. The institutional review board–approved consent forms were administered by members of our research team to the eligible individuals. These forms described the study, the measures used by the researchers to protect the confidentiality of the responses, and the voluntary nature of the study. The consent forms were countersigned by members of the research team, and copies were provided to the study participants.

### Data Entry and Quality Assurance

Data entry was performed by a team of field-workers and data management personnel. To ensure efficiency and high-quality data collection and processing, we (1) used a well-trained team of field-workers, (2) used a clearly defined study manual, (3) conducted weekly meetings with the research team, and (4) maintained logs of all patient contacts. To ensure efficient and accurate data management, we maintained (1) logs of all of the data instruments that were filled during each visit for every patient, (2) central data processing, and (3) weekly data checks. Data security was ensured through regular backups, password protection, and storage in a locked file cabinet.

### Variables Assessed

#### Sociodemographics

Baseline data were gathered on study participants’ age, income level, employment status, education level, smoking status, and alcohol consumption. Information was also collected on computer usage, internet usage, the frequency of computer and internet usage, and sources of health information.

#### Health Literacy

Health literacy is defined as “the ability to perform basic reading and numerical tasks required to function in the health care environment” [17]. Health literacy was assessed by using a 3-item health literacy screening questionnaire [17]. The questions included the following: (1) “How often do you have someone (like a family member, friend, hospital/clinic worker or caregiver) help you read hospital materials,” (2) “How often do you have problems learning about your medical condition because of difficulty understanding written information” (problems reading), and (3) “How confident are you filling out forms by yourself” (confident with forms)? Responses were rated on a Likert scale ranging from 0 to 4 and included the following options: “all of the time,” “most of the time,” “some of the time,” “a little of the time,” and “none of the time” [17].

#### Anthropometry

Height, weight, and waist circumference were measured by using a standard technique [18]. BMIs were computed from the height and weight measurements.

#### Physical Activity Assessment

All participants completed a validated short form of the International Physical Activity Questionnaire in order to calculate the total time that they spent on performing various forms of physical activity—recreational activities, occupational activities, household work, and transportation-related activities—in the last 7 days [19]. Total weekly physical activity—metabolic equivalents of task (METs; MET hours per week)—will be calculated as the weighted sum of the reported time spent at each intensity by using a MET value specific to each category (walking: 3.3 METs; moderate: 4 METs; vigorous: 7 METs) [19].

### Outcomes

The study outcomes include dietary KAPs. These outcomes were assessed by using the following tools. Satisfaction with medical care was also assessed.

#### Nutrition Knowledge Scale

The Nutrition Knowledge Scale comprises the following four types of items: (1) 10 items on the relationship between diet and disease, (2) 10 items on food comparisons in terms of their nutrient content (eg, fat, fiber, calcium, calories, and sodium); (3) 6 items on the daily serving requirements of different food groups; and (4) 5 items on weight and weight loss. The scale is in a multiple-choice format, and 1 point is awarded for correct answers; otherwise, 0 points are awarded. The interitem reliability (Cronbach α coefficient) of the Nutrition Knowledge Scale is .78 [20].

#### Nutrition Attitude Scale

The Nutrition Attitude Scale consists of 19 items and the following three sections: (1) care about nutrition (8 items), (2) emotional eating (6 items), and (3) the importance of nutrition (5 items). The response options are rated on a 5-point Likert scale and include “strongly disagree,” “disagree,” “neutral,” “agree,” and “strongly agree.” Reverse sentence items are scored reversely. The Cronbach α coefficient of the Nutrition Attitude Scale is .73 [20].

#### Nutrition Behavior Scale

The Nutrition Behavior Scale is a 24-item scale with responses on a 5-point Likert scale. It comprises the following two sections: (1) food selection and care about nutrition (15 items) and (2) emotionally and externally cued eating (9 items). The response items include “never,” “seldom,” “sometimes,” “often,” and “always,” ranging in score from 1 to 5. Reverse sentence items are scored reversely. The Cronbach α coefficient of the Nutrition Behavior Scale is .76 [20].

#### Satisfaction With Medical Care

Satisfaction with medical care will be measured by using the Client Satisfaction Questionnaire-8 (CSQ-8). The CSQ-8 is an 8-item questionnaire in which items are rated by using a 4-point Likert scale [21].

#### Blood Sugar Testing

We will also assess participants’ blood sugar levels at baseline and at 6 months to assess the pattern of blood sugar control.

### Data Analysis Plan

In the first step of the exploratory analysis, we will present a table to summarize the overall characteristics of all variables, including outcome, confounding, and process variables. This table will also serve as quality control for the original data and be used to mine missing data patterns and outliers. The distributions of the continuous outcomes will be explored for normality, and transformations will be used if necessary. Continuous variables will be summarized using means, medians, SDs, and ranges, while categorical variables will be examined by using frequencies and percentages. An exploratory analysis on process variables will be used for a post hoc analysis. As a third step, we will cross-tabulate the group assignments against outcome variables to assess the association in the initial stage of the study.

### Sample Size Justification

The sample size calculation was based on knowledge, attitude, and behavior outcomes, as reported in previous studies [22]. To detect a mean change of 0.2 with an SD of 0.7 at a 2-sided .05 α level of significance and a power of 85%, a sample size of 200 individuals in each group is needed. The total participant sample size will be 800.

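### The single planning pair (mean change 0.2, SD 0.7) does not plausibly fit the knowledge score and fits the attitude and behavior scales poorly, so the stated power for these outcomes is unsupported in their own metrics

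*Protocol article*

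**What the plan says.** The Sample Size Justification of the protocol article rests one calculation on three outcomes: "The sample size calculation was based on knowledge, attitude, and behavior outcomes". The inputs are a single pair: "To detect a mean change of 0.2 with an SD of 0.7". The test is set "at a 2-sided .05 α level of significance" with 85% power. The result is 200 per group and 800 in total. No unit, scale or per-outcome figure is given, and it is not said whether 0.7 is the SD of a score or of a change.

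The Outcomes section describes three different instruments:

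- **Knowledge:** four blocks of 10, 10, 6 and 5 items. "The scale is in a multiple-choice format, and 1 point is awarded for correct answers; otherwise, 0 points are awarded". On reliability: "The interitem reliability (Cronbach α coefficient) of the Nutrition Knowledge Scale is .78".
- **Attitude:** 19 items with five response options and alpha .73.
- **Behavior:** "The Nutrition Behavior Scale is a 24-item scale with responses on a 5-point Likert scale". Items score 1 to 5, with alpha .76.

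For none of the three does the article say whether the score is a total or a mean, and it gives no SD for any of them. The Statistical Analysis section lists these outcomes among the primary ones. The Results section reports 400 per arm, made up of 200 per arm in each of the urban and rural settings.

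**The concern.** A difference and an SD have meaning only on a stated metric. One pair can serve three scales only if all three share a metric and have similar spread, or if the pair is really a standardised effect. The article claims neither, and a 0/1 knowledge score does not share a metric with 5-point Likert items.

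At stake is what the trial was sized to detect. If the pair fits none of the scales as scored, the reader cannot tell which difference in knowledge, attitude or behavior the 85% refers to. A null result on any of them would then be hard to interpret.

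**Working it through.** **1. The plan's own figure.** Inputs from the Sample Size Justification: difference 0.2, SD 0.7, two-sided alpha 0.05, power 85%.

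n per group = 2 × (1.960 + 1.036)² × (0.7/0.2)² = 2 × 8.98 × 12.25 ≈ 220 (221 with the t distribution). The stated figure is 200.

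Power with 200 per group: 0.2 / (0.7 × √(2/200)) = 2.857, and Φ(2.857 − 1.960) = 81.5%. With 400 per group: 0.2 / (0.7 × √(2/400)) = 4.041, and Φ(4.041 − 1.960) = 98.1%.

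Variants do not recover 200 from the stated inputs. One-sided testing gives 177, 80% power gives 193, and a single-group or paired change gives 110. A change score with SD 0.7 per visit gives 198, but only with an assumed correlation of 0.55 that the article does not state.

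**2. Knowledge as a proportion correct (0 to 1).** The SD of a score confined to 0-1 is at most √(0.5 × 0.5) = 0.5. An SD of 0.7 at one visit is impossible.

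**3. Knowledge as a total (0 to 31).** For k items scored 0/1, with p the proportion correct and q = 1 − p, the definition of alpha gives

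Var(total) = Σpq / (1 − alpha × (k − 1)/k).

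With k = 10 + 10 + 6 + 5 = 31 and alpha .78, the divisor is 1 − 0.78 × 30/31 = 0.2452. An SD of 0.7 is a variance of 0.49, so Σpq = 0.49 × 0.2452 = 0.120. The mean pq is 0.120/31 = 0.0039. With equal item difficulty, p ≈ 0.996 or 0.004. At the upper end the mean is 31 × 0.9961 = 30.88, which leaves 0.12 points of room, less than the 0.2 to be detected.

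Two more lenient readings:

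- Ignore alpha and assume only that the average inter-item covariance is not negative. Mean pq is then at most 0.49/31 = 0.0158, so p is at least 0.984 or at most 0.016.
- Take 0.7 as the SD of a change, in the most favourable case where only measurement error varies. The score SD is 0.7/√(2 × 0.22) = 1.06, and p ≈ 0.991 (or 0.009).

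**4. Attitude and behavior.** The same identity applies. As item means, the required item SD is 0.7 × √(k × divisor). Items are taken as scored 1-5; the article states this for behavior, and it is assumed for attitude. The largest possible item SD is then 2.

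| Scale | k | alpha | Divisor | Item SD needed for an item-mean SD of 0.7 | Item-mean SD if item SD = 1 (assumed) | Total SD if item SD = 1 (assumed) |
|---|---|---|---|---|---|---|
| Attitude | 19 | .73 | 0.308 | 1.69 | 0.41 | 7.8 |
| Behavior | 24 | .76 | 0.272 | 1.79 | 0.39 | 9.4 |

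An SD of 0.7 needs nearly the widest possible item spread if the scales are item means, and is far too small if they are totals.

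**5. Consequence for knowledge if 0.2 means raw points on 0-31.** Assume equal item difficulty with 50% to 90% correct, and the quoted alpha. SD = √(31pq/0.2452).

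| Assumed % correct | SD (points) | Power for 0.2, 200 per arm | Power for 0.2, 400 per arm | n per arm for 85% | 0.286 SD in points |
|---|---|---|---|---|---|
| 50 | 5.6 | 6.5% | 7.9% | 14,192 | 1.6 |
| 70 | 5.2 | 6.7% | 8.5% | 11,921 | 1.5 |
| 90 | 3.4 | 9.1% | 13.4% | 5,109 | 1.0 |

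**6. Consequence if the ratio was meant.** 0.2/0.7 = 0.286 SD. The powers in step 1 then apply to any scale: 81.5% at 200 and 98.1% at 400 per arm.

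**The case against.** The strongest reply is that power depends only on the ratio of difference to SD. The article gives no unit, so 0.2 and 0.7 may stand for a standardised effect of 0.286, and power at 400 per arm would be about 98% on every scale. This stands. A reader might infer that the trial has power below 15% for knowledge, but the documents do not support that as a finding. It follows only if 0.2 is read as raw points on the 0-31 total and an inferred SD replaces 0.7.

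A second reply is that the inputs come from an earlier study that cannot be checked here, and that the SD may belong to a change. This stands in part. A change in a proportion runs from −1 to 1, so its SD can reach 1 and the 0.5 ceiling does not bind. On the 0-31 total, too, 0.7 is implausible rather than impossible. A reader might say that the pair cannot describe the knowledge score at all. That holds only for a proportion at a single visit.

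A reader might also infer that knowledge is the exception and that the pair suits the Likert scales. The article's own alphas do not bear that out, as step 4 of the working shows.

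Finally, all 800 participants are enrolled, so no recruitment decision depends on this. That is true, but how the result is interpreted still does.

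**Conclusion.** The point holds as a mismatch between a stated planning input and the stated scoring. The pair does not plausibly describe the knowledge score under either natural scoring, and it fits attitude and behavior poorly. The 85% is therefore unsupported in the scales' own metrics; it has not been shown that each scale lacks adequate power.

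The size depends on what was meant. With 0.286 SD, the shortfall is modest and arises only at 200 per arm, that is, within one setting: 81.5% instead of 85%. The full comparison at 400 per arm is well powered. With 0.2 raw points on the 0-31 total, power is about 6-9% at 200 and 8-13% at 400 per arm.

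The conclusion rests on the quoted alphas applying to this population and, for the percentages correct, on equal item difficulty. The raw-point powers also rest on an assumed 50-90% correct. The failure of the stated inputs to give 200 per group needs none of these assumptions.

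**What to change.** Rewrite the Sample Size Justification paragraph as follows.

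1. State the planning assumption as a standardised difference of 0.286. Give the power that follows: about 81% at 200 per arm within an urban or rural stratum and 98% at 400 per arm overall. Correct either the 200 or the 85%, since 85% needs about 220 per group.
2. State for each of the three scales whether it is scored as a total or a mean.
3. From the baseline data on the 800 participants, pooled over arms, give the SD of each scale in that metric and the difference detectable with 85% power: 2.996 × √(2/400) = 0.212 SD at 400 per arm, and 2.996 × √(2/200) = 0.300 SD at 200 per arm within stratum.
4. Note that the SD of a change may differ from the baseline SD, so these detectable differences are approximate if change is analysed.

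The cost is a short calculation on data already collected and one revised paragraph. This assumes that the baseline knowledge, attitude and practice data were gathered with the scales in the Outcomes section. No extra participants and no follow-up data are needed.

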### Study Groups

The study participants were randomly assigned into the following two groups: the intervention group (telephone-linked dietary decision support system) and the control group (paper-based diet record; Figure 1). The randomization was conducted following the assessment of participants’ eligibility for inclusion in the study. Study participants in the intervention group (group 1) recorded their daily dietary intake by using a telephone-linked, personalized, human-centered dietary decision support system and received personalized feedback and diet education via SMS text messaging. The personalized, human-centered dietary decision support system is a telephone-linked decision support system designed to provide tailored dietary education to patients with diabetes. The study participants were able to access the personalized, human-centered dietary decision support system through their computers, cell phones, or a telephone-linked service, depending on the technology platform available to them. The telephone-linked service enabled the participants (including those who did not have a technology platform to access the personalized, human-centered dietary decision support system) to receive phone calls from our research team in order to record their daily dietary intake. The personalized, human-centered dietary decision support system also generated automatic alerts that served as reminders to the participants who had not reported their daily diet intake. Study participants in the control group were provided with a paper-based diet record for documenting their daily dietary intake. Both the intervention group and control group were provided with a diabetes educational booklet at baseline. However, the study participants in the control group were also provided with a booklet to document their diet log on a daily basis. Follow-up visits were conducted at 3 and 6 months from the baseline in both groups. Baseline data were gathered on sociodemographics; health literacy; physical activity; anthropometric measurements; blood sugar testing; and diabetes knowledge, attitudes, and practices (KAPs). Follow-up data were gathered on anthropometric measurements, diabetes KAPs, blood sugar testing, and satisfaction with medical care.

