## Results

Data collection was conducted between the period of June and December 2018. The collection of baseline data from 800 study participants in both the intervention (n=400) and control groups (n=400), which were stratified by urban (control group: n=200; intervention group: n=200) and rural settings (control group: n=200; intervention group n=200), has been completed. Follow-up data collection for months 3 and 6 is ongoing. We expect the follow-up data collection to be completed by October 2019. We are currently analyzing the baseline data and generating reports, which will be presented in our upcoming manuscript.

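### On the stated inputs, 200 per group gives about 81% power, not 85% (which needs 220 to 221), and the 200 fits only an arm within one setting

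*Protocol article*

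**What the plan says.** The Sample Size Justification section gives a full set of inputs. The target is set out as "To detect a mean change of 0.2 with an SD of 0.7", tested "at a 2-sided .05 α level of significance". From these it concludes that, for "a power of 85%, a sample size of 200 individuals in each group is needed". The next sentence gives the total: "The total participant sample size will be 800". No step links the 200 to the 800.

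Elsewhere, group means a randomised arm. Under Study Groups: "The study participants were randomly assigned into the following two groups", namely the decision support system and the paper record. The Statistical Analysis section uses the word in the same way. The Results section reports "800 study participants in both the intervention (n=400) and control groups (n=400", and describes them as "stratified by urban (control group: n=200; intervention group: n=200) and rural settings", with the same 200 and 200 in the rural setting.

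**The concern.** There are two linked faults. First, the stated power and the stated sample size do not agree on the section's own inputs. Second, the 200 is attached to a word that everywhere else in the article means an arm of 400. A reader therefore cannot tell whether the 85% describes the comparison within one setting or the pooled comparison of the two arms, and the figure is wrong for both: too high for the first and too low for the second.

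What is at stake is interpretation. The article expects urban-rural differences across the groups. If an urban-only or rural-only comparison is reported and is null, it could be read as coming from a test with 85% power when the figure on these inputs is nearer 81%, and lower after any losses.

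**Working it through.** **Inputs** (all from the Sample Size Justification, except the arm and cell sizes, which are in Results): difference d = 0.2; SD s = 0.7; two-sided alpha .05 (z = 1.960); power 85% (z = 1.0364); stated n = 200 per group; enrolled 400 per arm, 200 per arm in each setting. The section does not say whether 0.2 is a between-group difference or a within-group change. The check takes it as a between-group difference, because the section sizes each group, and tests the other reading below.

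**Attempt to reproduce the stated 200.** For two independent means:

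n per group = 2 x (1.960 + 1.0364)^2 x (s/d)^2 = 2 x 8.978 x (3.5)^2 = 2 x 8.978 x 12.25 = 219.97, so **220**.

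The t-test version gives 220.9, so **221**. The stated 200 is about 9% below 220 (20/220).

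**Other readings of the stated inputs:**

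| Reading | n per group |
|---|---|
| One-sided .05, 85% power | 177 |
| Two-sided, 80% power | 193 (194 by t-test) |
| Two-sided, 90% power | 258 |
| One-sample or paired change, 85% power | 110 (112 by t-test) |
| Rank test, efficiency 0.955 (220/0.955) | 231 |

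None gives 200. Reaching 200 at 85% power needs an input that the section does not state: an SD of about 0.667, a difference of about 0.21, or adjustment for a baseline value with correlation of about 0.3 (220 x (1 - 0.3^2) = 200.2).

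**Power at the stated and enrolled sizes** (power = Phi[d / (s x sqrt(2/n)) - 1.960]):

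- 200 per arm: 0.2 / (0.7 x 0.1) = 2.857; 2.857 - 1.960 = 0.897; power **81.5%** (81.3% by t-test).
- 400 per arm: 0.2 / (0.7 x 0.0707) = 4.041; 4.041 - 1.960 = 2.081; power **98.1%** (98.1% by t-test).

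**What the 200 refers to.** Two groups of 200 would make 400. The Results section gives four cells of 200: intervention and control, urban and rural. So 2 arms x 2 settings x 200 = 800, and the 200 matches an arm within one setting.

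**The case against.** The strongest reply is that the gap is small and does not reach the main comparison. The article randomises to two arms of 400, which gives about 98% power on these inputs. A shortfall of about 3.5 points within one setting would be closed by a modest baseline adjustment. The first part stands, and it limits the seriousness of the point. The second does not rescue the text, because no such adjustment is stated in the calculation.

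Three stronger readings are tempting, and the documents do not support them.

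- *The total of 800 is unexplained.* The Sample Size Justification omits the link, but the Abstract and Results supply it through the four cells of 200. What remains is unclear wording, not a total that fails to add up.
- *The missing dropout allowance is an error.* A condensed article may leave this to the full protocol, and no loss rate is given. Purely as an assumption, 10% or 20% loss would take 200 per arm to 180 or 160, with about 77% or 72% power. From 400 per arm, even 45% loss leaves 220 and 85% power.
- *No analysis uses the settings separately.* The first specific aim compares urban and rural participants, and the Discussion expects differences by setting. The Statistical Analysis section names no within-setting treatment test, but that detail may sit in a document not shown.

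A further fair point is that power for a comparison of means does not carry over to the log-rank test and Cox model named for the primary outcomes. This also limits any restated figure, so the correction should say so.

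**Conclusion.** The point holds in limited form. The Sample Size Justification contains a wrong figure: on its own inputs, 85% power needs 220 to 221 per group, and 200 gives about 81%. The figure is attached to an ambiguous unit, since group elsewhere means an arm of 400.

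A reader might infer that the trial as a whole is underpowered. The article does not support that: the pooled two-arm comparison has about 98% power on the same inputs. The overstatement applies only within one setting.

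The conclusion assumes that 0.2 is a between-group difference, that 0.7 is the SD of the quantity compared in each arm, that the test is an unadjusted comparison of two means, and that there are no losses. The paired reading does not return 200 either. This is a stated figure that should be corrected, with limited consequence for the main comparison.

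**What to change.** Keep the total of 800 and revise the Sample Size Justification as follows:

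1. Remove the 85% claim.
2. Say that 200 is the number per arm within each setting, so that two arms and two settings give 800.
3. Restate power for a difference of 0.2 with SD 0.7 at two-sided .05, before any losses: about 81% within one setting (200 per arm) and about 98% for the pooled comparison (400 per arm).
4. State which of these two comparisons the calculation is meant to support. That choice belongs to the authors.
5. Add that the figures apply to a comparison of means and not to the log-rank test named under Statistical Analysis.

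The cost is wording only. The within-setting figure becomes slightly less favourable. Baseline enrolment of 800 is already complete, and no extra participants are needed.
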